## Background

Peritoneal dialysis (PD) is a well-established treatment modality of home renal replacement therapy (RRT) for end-stage kidney disease (ESKD) patients and has been available in Thailand for more than three decades. Although technical innovations and improvements in PD practice have significantly decreased PD-associated adverse outcomes, PD-related infections, including PD-related peritonitis and exit-site/tunnel infection, are still the most common complications [1–3]. From the patient/caregiver and healthcare professional’s perspectives, PD-related infection is the highest priority outcome in PD treatment [4, 5]. Moreover, PD-related peritonitis is the leading cause of long-term structural and functional peritoneal membrane malfunction [1, 6]. As a result, substantial PD technique failure, hospitalizations, mortality, and healthcare costs are responsible for the limited modality options as an RRT and limited long-term PD use [1–3, 6].

Several strategies involve topical antimicrobial agents to prevent PD-related infections and are being widely used [7]. Of these, daily exit-site care with mupirocin cream or ointment is the most common approach, targeting the exit-site infections caused by *Staphylococcus aureus*. This strategy has been proven to be effective by several existing observational studies, randomized controlled trials (RCTs), and meta-analyses and is recommended by the International Society for Peritoneal Dialysis (ISPD) guidelines [7–13]. Regarding antimicrobial activity, mupirocin is only effective against gram-positive organisms, primarily *S. aureus*. Nevertheless, the emergence of mupirocin resistance has been reported in the long-term application of exit-site care in recent years [14–16].

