Chlorhexidine is a water-soluble cationic biguanide with broad-spectrum properties, including antimicrobial effects against gram-positive and gram-negative bacteria, facultative anaerobes and aerobes, and yeast, and it inactivates some viruses [17]. Recently, several controlled trials have revealed that preoperative skin preparation and skin decolonization with chlorhexidine gluconate decreases the rates of surgical-site infections, healthcare-associated infections and bacterial transmission in noncritically and critically ill patients [18–21]. Among PD patients, topical 0.05% to 4% chlorhexidine gluconate aqueous solution, with or without isopropyl alcohol, also commonly has been used in previous practice [22–24] and is recommended by the ISPD guidelines [7]. Chlorhexidine is safe and poorly absorbed through intact adult skin [17]. Nevertheless, the daily application of chlorhexidine gluconate for exit-site care may induce local skin irritation, which could limit patient acceptability and long-term compliance. Whether local irritability limits the long-term and widespread use of chlorhexidine gluconate remains uncertain.

In addition to the ISPD recommendations, two comparative observational studies [25, 26] and one RCT [22] have suggested that exit-site care with normal saline is well tolerated and may be an alternative strategy for the prevention of PD-related infections. The results of these studies revealed that normal saline was not superior or more beneficial than other agents for preventing exit-site infections. However, evidence of exit-site care with normal saline dressing was insufficient and remains unclear.

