### Interventions

All participants will be required to perform daily washings of the exit site with antibacterial soap while showering, followed by drying of the exit site using a sterile gauze pad. Once-daily usual exit-site care dressing with normal saline will be performed for all participants before application of the randomly assigned fixed-order interventions, as follows: (i) chlorhexidine gluconate-impregnated patch plus placebo ointment base or (ii) placebo sterile patch plus mupirocin ointment or (iii) both placebo sterile patch and placebo ointment base. Participants who were *S. aureus* nasal carriers (within 4 weeks in the screening period) will be decolonized with 2% mupirocin ointment applied to both anterior nares twice daily for 5 consecutive days before the trial starts. All medications administered as a part of standard PD care will be allowed. Details of the investigational medicinal products (IMPs) and their administration are provided in Table 2 and Additional file 2: Appendix 1. Participants will record the use of IMPs with adherence, which will be monitored by their return of the relevant packaging (plastic sachets and ointment tubes).

**Table 2 Tab2:** IMPs in the COSMO-PD trial

Intervention	Chlorhexidine gluconate	Mupirocin ointment	Usual care with normal saline dressing
Description of IMPs	Non-ionized cloth impregnated with 2% chlorhexidine gluconate (Ion PAD PLUS CHG2®, Pose Health Care., Ltd.)	2% mupirocin calcium ointment (Charoon Bhesaj Co., Ltd.)	Isotonic solution, 0.9% sodium chloride irrigation USP (A.N.B. Laboratories Co., Ltd.)
Packaging	Non-rinse, disposable, single use in plastic sachet	5-g ointment tube	Plastic bottle container 500 mL, sterile and non-pyrogenic
Dummy placebo	Identical placebo ointment tube	Identical plastic sterile non-ionized patch sachet	Identical both placebo ointment tube and placebo plastic sterile non-ionized patch sachet
Administration	Wiping over PD catheter exit site after dressing with normal saline solution, then applying with placebo ointment base by participants or their caregivers, once daily.	Daily applying to PD catheter exit site by participants or their caregivers after dressing with normal saline and wiping with placebo sterile non-ionized patch, respectively	Daily dressing exit site with normal saline solution by participants or their caregivers, then wiping with placebo sterile non-ionized patch and applying with placebo ointment base, respectively

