### Outcomes

#### Primary outcome

The primary outcomes of the COSMO-PD trial are time-to-first PD-related infection (exit-site/tunnel infection or peritonitis) event and overall difference in PD-related infection rates between study arms. PD-related peritonitis and exit-site/tunnel infection will be defined according to the ISPD guidelines [2, 7]. Participants will be diagnosed as having peritonitis if they meet at least two of the following criteria: (i) clinical features (e.g., abdominal pain and/or cloudy dialysis effluent); (ii) dialysate effluent white cell count more than 100 cell/μL (after a dwell time of at least 2 h), with polymorphonuclears making up more than 50%; and (iii) positive dialysis effluent culture. Exit-site infection and tunnel infection will be indicated as the presence of purulent discharge (with or without erythema of the skin) and evidence of collection along the catheter tunnel (clinical inflammation or ultrasonographic), respectively.

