To address robustness of the treatment effects, further sensitivity analyses of the primary analysis will be performed by (i) adjusting for the several baseline covariates that seem to affect the outcomes (age, history of diabetes, history of PD-related infections, *S. aureus* colonization status, PD modality, PD vintage, and serum albumin); (ii) restricting the analysis to only PD-related infection episodes with positive cultures to account for misclassification bias; (iii) using the proportional sub-distribution hazards analyses by Fine and Gray method to address the completing risk outcomes, including mode switching to long-term hemodialysis, kidney transplantation, conservative treatment, or death; and (iv) using the multiple imputation method to evaluate the effect estimates when missing data are indicated.

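### The culture-positive sensitivity analysis can under-count exit-site infection more in the active arms, because the randomised product may suppress the culture the filter relies on

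*Protocol article*

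**What the plan says.** All references are to the protocol article.

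- **Statistical analysis.** Four sensitivity analyses are listed to test how robust the primary treatment effects are. The second is "restricting the analysis to only PD-related infection episodes with positive cultures to account for misclassification bias". It applies to the whole composite, with no distinction between components.
- **Primary outcome.** Peritonitis needs two of three criteria, one of which is "positive dialysis effluent culture". The other component has no culture criterion: "Exit-site infection and tunnel infection will be indicated as the presence of purulent discharge (with or without erythema of the skin" is the start of its definition, which then gives clinical or ultrasound evidence of a collection for tunnel infection.
- **Interventions and Table 2.** The arms receive "chlorhexidine gluconate-impregnated patch plus placebo ointment base or (ii) placebo sterile patch plus mupirocin ointment or (iii) both placebo sterile patch and placebo ointment base". The patch is used by "Wiping over PD catheter exit site after dressing with normal saline solution", and the ointment is applied to the same place, once daily for 24 months. Every participant also performs "daily washings of the exit site with antibacterial soap while showering".
- **Background.** Chlorhexidine is described as broad-spectrum, "including antimicrobial effects against gram-positive and gram-negative bacteria", whereas "mupirocin is only effective against gram-positive organisms".

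**The concern.** For peritonitis the restriction is natural: the culture is already a diagnostic criterion, and the sample is effluent, not treated skin. For exit-site infection it adds a filter that the outcome definition does not contain. That filter is a measurement made after randomisation, at the site where the randomised product acts. Residual chlorhexidine or mupirocin could turn the culture of a genuine infection negative, and the placebo products have no such effect. True exit-site episodes would then be discarded more often in the active arms.

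At stake is how a robustness check is read. An analysis introduced to deal with misclassification could itself misclassify by arm, in the direction that favours the active products. The chlorhexidine-versus-mupirocin comparison is exposed too, because the two spectra differ.

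**Working it through.** The article states no culture yield and no result for this analysis, so there is no figure of the plan's own to reproduce. The effect can only be bounded.

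**Inputs from the article (Sample size and power calculations):** exit-site infection 0.31 and peritonitis 0.39 episodes per patient-year, composite 0.70. Peritonitis is therefore 0.39/0.70 = 56% of expected control-arm episodes and exit-site infection 44%. The design rate ratio is 0.49/0.70 = 0.70.

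**Assumptions, not in the article:** the culture for an exit-site episode is taken at the exit site. Let s0 and s1 be the probabilities that a true exit-site episode is culture-positive on saline and on active treatment. Let sp be the same for peritonitis, equal in all arms. The true rate ratio RR is the same for both components.

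**Formulas**

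- Composite: apparent ratio = RR × (0.31·s1 + 0.39·sp) / (0.31·s0 + 0.39·sp)
- Exit-site component alone: apparent ratio = RR × s1/s0

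**No true effect (RR = 1), s0 = 0.85, sp = 0.80.** The saline culture-positive rate is 0.31 × 0.85 + 0.39 × 0.80 = 0.2635 + 0.3120 = 0.5755.

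| s1 | Active culture-positive rate | Composite ratio | Exit-site ratio |
|---|---|---|---|
| 0.85 | 0.5755 | 1.00 | 1.00 |
| 0.75 | 0.2325 + 0.3120 = 0.5445 | 0.95 | 0.88 |
| 0.65 | 0.2015 + 0.3120 = 0.5135 | 0.89 | 0.76 |
| 0.55 | 0.1705 + 0.3120 = 0.4825 | 0.84 | 0.65 |

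**Other assumed yields, s1 lower by 10, 20 and 30 points**

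| s0, sp | Composite, true 1.00 | Composite, true 0.70 |
|---|---|---|
| 0.90, 0.85 | 0.95, 0.90, 0.85 | 0.66, 0.63, 0.59 |
| 0.80, 0.80 | 0.94, 0.89, 0.83 | 0.66, 0.62, 0.58 |

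The size of the artefact depends mainly on the gap between s0 and s1 and little on their level.

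**Between the active arms.** Suppose, as an illustration only, that yield falls by 20 points on chlorhexidine and by 10 on mupirocin, because mupirocin leaves gram-negative growth untouched. From the first table, a true ratio of 1.00 for chlorhexidine against mupirocin appears as 0.5135/0.5445 = 0.94. The article does not say which product would suppress cultures more in practice.

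**The case against.** The strongest reply is that nothing in the article shows a lower yield. It gives no culture results and does not describe how discharge is cultured, which a full protocol may well do. A reader might infer that the analysis certainly introduces bias; the documents support only that it can.

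A reader might also infer that only the active arms have an antibacterial on the skin. That is wrong, since all arms wash with antibacterial soap. The soap may lower yield everywhere, but it does not remove the difference made by the randomised product.

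A third tempting reading is that the analysis could manufacture a confirmed benefit out of nothing. The primary analysis needs no exit-site culture. With equal infection rates it would be expected to show no benefit, and one seen only in the culture-positive analysis would be a visible discordance. What stands is narrower: an effect already seen in the primary analysis could look larger or firmer than it is.

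Finally, exit-site infection is the component with a purely clinical definition, so culture confirmation is arguably most useful there, and dropping it would give up specificity. This stands as a reason to keep the analysis. It is partly answered by the definition itself, which requires purulent discharge; the skin-reaction grades under Safety monitoring and trial-related injury do not include it.

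**Conclusion.** The concern holds as a risk of unknown size. The restriction handles misclassification without bias only if culture yield among true exit-site episodes is equal across arms, and the plan attaches no such condition to it. Any suppression by the randomised product would favour the active arms, and could do so unequally for the two products.

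Under assumed yields of 85% for exit-site infection on saline and 80% for peritonitis, with exit-site yield 10 to 30 points lower on active treatment, a null composite rate ratio appears as 0.95 to 0.84. A true 0.70 appears as about 0.66 to 0.58 over the other yield sets tried. Peritonitis dilutes the effect, and these composite figures already allow for that. Equal yields give no bias.

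The primary analysis and the sample size are untouched. Missing swab instructions are not part of this point, since an article may leave them to the full protocol.

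**What to change.** Keep the analysis and change how it is reported:

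1. Report it separately for peritonitis and for exit-site/tunnel infection.
2. Tabulate, by arm, the share of clinical exit-site episodes that are culture-positive, with confidence intervals.
3. Add a version that applies the culture restriction to peritonitis (effluent) only and leaves exit-site/tunnel infection on the definition in the Primary outcome section.
4. State that the composite culture-positive result will not be read as free of misclassification unless yield is similar across arms.

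Step 2 is descriptive and not very precise. At the planning rate, 118 participants followed for the full two years give 118 × 2 × 0.31 = 73 exit-site episodes. With both shares at the assumed 85% and episodes treated as independent, the 95% half-width for the difference is 1.96 × √(2 × 0.85 × 0.15/73) = 0.12. Similar observed shares would thus not exclude a 10-point gap, which is why step 3 is needed as well.

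The cost is one more analysis and one more table, with no extra samples. The added version is not culture-confirmed for exit-site infection, so it should stand beside the existing analysis and not replace it.

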**Fig. 2 Fig2:**
[figure not shown]
A simplified Markov model structure of the COSMO-PD trial

### Ethics and regulatory aspects

The COSMO-PD trial will be conducted according to the standards of the International Conference on Harmonization-Good Clinical Practice. Pharmacovigilance reporting will comply with the 2004 Medicines for Human Use (clinical trials) Regulations and 2006 Amended Regulations. We will conduct the investigation in accordance with the key principles of ethical conduct in research and the Declaration of Helsinki. The sponsors will not be involved with study design, or data assembly and analysis.

#### Informed consent

Participants will be included in the study only if they provide written informed consent. Participant consent will be obtained by trained research assistants (Additional file 2: Appendix 2). Written informed consent will be provided by all participants prior to randomization. If a participant is illiterate, a thumbprint will be required on the consent form in line with the International Conference on Harmonization: Thai Guideline for Good Clinical Practice. Informed consent may be withdrawn at any time during the study period and will have no effect on a participants’ clinical management at the study site.

#### Confidentiality

Consented participants will be assigned a screening number and a study identification code number that will be the primary mode of identification throughout the study. Subsequently, unique identifiers will be generated for computer-based data entry and all specimens. All information collected will remain confidential and shared only within the research study team. Initial screening forms, case report forms, and completed identification code number list will be kept in locked files.

#### Healthcare services and reimbursement

Participants unwilling to participate or who cannot be enrolled into the study due to unmet criteria will be referred for standard protocol for exit-site care at each setting. A clear statement will be provided to indicate that the decision not to participate in the trial will not affect subsequent care. Participants in the trial will be reimbursed for their transport to attend all follow-up visits at the study site (500 Thai baht/visit). No other gifts or payments will be offered.

### Study withdrawal

Participants may withdraw from the trial at any time for any reason. Furthermore, participants who meet any of the following conditions will be allowed to withdraw from the trial: (i) refusing to follow the study protocol; (ii) using other IMPs; (iii) pregnancy during the study period; (iv) switching mode to long-term hemodialysis, kidney transplantation, or conservative treatment; and (v) developing serious adverse drug reactions or suspected unexpected serious adverse reactions. According to the intention-to-treat approach, data collected prior to study withdrawal will be considered for participants who discontinue or deviate from the assigned intervention protocols.

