**Methods/Designs:**

This study is a randomized, double-blind, multicenter, active-controlled, clinical trial. Adult patients aged 18 years or older who have end-stage kidney disease and are undergoing PD will be enrolled at three PD Centers in Thailand. A total of 354 PD patients will be randomly assigned to either the 2% chlorhexidine gluconate-impregnated patch, mupirocin ointment, or usual exit-site care with normal saline dressing according to a computer-generated random allocation sequence. Participants will be followed until discontinuation of PD or completion of 24 months. The primary study outcomes are time to first PD-related infection (exit-site/tunnel infection or peritonitis) event and the overall difference in PD-related infection rates between study arms. Secondary study outcomes will include (i) the rate of infection-related catheter removal and PD technique failure, (ii) rate of nasal and exit-site *Staphylococcus aureus* colonization, (iii) healthcare costs, and (iv) skin reactions and adverse events. We plan to conduct a cost-utility analysis alongside the trial from the perspectives of patients and society. A Markov simulation model will be used to estimate the total cost and health outcome in terms of quality-adjusted life years (QALYs) over a 20-year time horizon. An incremental cost-effectiveness ratio in Thai Baht and U.S. dollars per QALYs gained will be illustrated. A series of probabilistic sensitivity analyses will be conducted to assess the robustness of the cost-utility analysis findings.

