#### Statistical analysis

Baseline characteristics will be summarized as number (percentage) or mean ± standard deviation, or medians with interquartile range as suitable. Differences between treatment groups will be compared using Fisher’s exact test and analysis of covariance (ANCOVA) or Kruskal-Wallis test for categorical and continuous variables, respectively. All analyses will be conducted on both a per-protocol and intention-to-treat basis. All analyses will be performed using Stata software version 14.0 (StataCorp, LP) and Microsoft Excel version 2016. They will be two-tailed, and a *P*-value less than 0.05 will be considered statistically significant.

For a primary analysis, Cox proportional hazards regression and Poisson regression analyses will be performed to assess the effectiveness of the chlorhexidine gluconate-impregnated patch and mupirocin ointment compared to usual exit-site care with normal saline for the first episode of PD-related infection and longitudinal rates, respectively. Secondary analysis using statistical methods as described above will then be analyzed to evaluate the effect on the prevention of PD-related infections between chlorhexidine gluconate-impregnated patch and mupirocin ointment. The treatment effects will be estimated as hazard ratios or incidence rate ratios with corresponding 95% confidence interval. Kaplan-Meier survival curves will be constructed for visual presentation of time-to-event comparisons.

Several a priori subgroup analyses with respect to the minimization variables for both primary and secondary outcomes will be investigated. For instance, the lists of variables include age (<65 vs. ≥65 years), gender, history of diabetes, history of PD-related infections (peritonitis or exit-site/tunnel infection), *S. aureus* colonization status (nasal or exit-site PD catheter), PD modality (continuous ambulatory peritoneal dialysis vs. automated peritoneal dialysis), PD vintage, and serum albumin (< 3.5 vs ≥3.5 mg/dL).

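### The intention-to-treat rule stops at study withdrawal and makes deviation and serious adverse reactions grounds for withdrawal, contrary to follow-up until PD ends or 24 months

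*Protocol article*

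**What the plan says.** The abstract (Methods/Designs) sets the follow-up: "Participants will be followed until discontinuation of PD or completion of 24 months". It makes no exception for a participant who stops or changes the product.

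The Study withdrawal section says that "participants who meet any of the following conditions will be allowed to withdraw from the trial". The list opens with "i) refusing to follow the study protocol; (ii) using other IMPs; (iii) pregnancy during the study period". Ground (iv) is a change to hemodialysis, transplantation or conservative treatment, and ground (v) is "developing serious adverse drug reactions or suspected unexpected serious adverse reactions". The section then gives its intention-to-treat rule: "data collected prior to study withdrawal will be considered for participants who discontinue or deviate from the assigned intervention protocols". It describes no collection of outcomes after such a withdrawal.

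Under Statistical analysis, "Cox proportional hazards regression and Poisson regression analyses will be performed" for time to first PD-related infection and for infection rates respectively. The same section states: "All analyses will be conducted on both a per-protocol and intention-to-treat basis". Its sensitivity analyses include a Fine and Gray model for modality switch, transplantation, conservative treatment or death, and multiple imputation if data are missing.

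**The concern.** Grounds (i), (ii) and (v) concern how a participant used or tolerated the product. None of them ends PD. A participant who leaves on one of these grounds may still have a catheter and may still develop an exit-site infection or peritonitis. Under intention-to-treat those infections belong to the assigned arm, but under the stated rule they are not counted.

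The Cox and Poisson models tolerate such censoring only if, given what is in the model, exit is unrelated to later infection risk. Refusing the regimen, turning to another product or reacting badly could each be related to that risk, and could occur at different rates by arm. If so, both primary outcomes lose some of the protection of randomisation. Follow-up that was never collected cannot be restored by a later analysis.

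**Working it through.** **1. The rules side by side.** The plan gives no figure for this point, so the first check is of the text.

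| Event | Abstract, Methods/Designs | Study withdrawal section |
|---|---|---|
| Refuses protocol, uses another study product, or has a serious adverse reaction; still on PD | Follow-up continues to end of PD or 24 months | May withdraw; only data before withdrawal are used |
| Stops PD (ground iv) | Follow-up ends | May withdraw; risk of PD infection has ended |

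The two rules agree on the second row and conflict on the first.

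**2. Do the sensitivity analyses cover the first row?** The Fine and Gray analysis lists modality switch, transplantation, conservative treatment and death. Grounds (i), (ii) and (v) are not among them. Multiple imputation is conditional on missing data being found, and the article does not say that it covers infections after withdrawal.

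**3. Illustration: selective exit with no true effect.** From Sample size and power calculations: control rate 0.70 per patient-year, design ratio 0.49/0.70 = 0.70, all-cause dropout 25%. Planned follow-up is 2 years.

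Assumptions, not in the documents: a share f = 0.25 leaves one active arm only, at time t years; nobody leaves control; leavers have k times the stayers' rate throughout; the true 24-month rate is 0.70 in both arms.

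- Stayers' rate: s = 0.70 / (1 − f + f·k)
- Truncated rate: s × [2(1 − f) + f·t·k] / [2(1 − f) + f·t]
- Spurious ratio: truncated rate / 0.70

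For k = 2, s = 0.70/1.25 = 0.56 and leavers' rate = 1.12.

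- Exit at month 12: (1.5 × 0.56 + 0.25 × 1.12) / 1.75 = 1.12/1.75 = 0.64; ratio 0.64/0.70 = 0.91.
- Exit at month 6: (1.5 × 0.56 + 0.125 × 1.12) / 1.625 = 0.98/1.625 = 0.603; ratio 0.603/0.70 = 0.86.

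| k | Exit at month 12 | Exit at month 6 |
|---|---|---|
| 0.5 | 1.06 | 1.10 |
| 1 | 1.00 | 1.00 |
| 1.5 | 0.95 | 0.92 |
| 2 | 0.91 | 0.86 |
| 3 | 0.86 | 0.77 |

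The bias is zero at k = 1 and reverses when leavers are at lower risk. It also cancels if the same share with the same k leaves both arms at the same time.

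**4. Illustration: rate changes after exit.** Let the active arm run at 0.49 while observed, with 25% leaving at month 12 and then having k times 0.49. The truncated ratio is always 0.70. The full-follow-up ratio is 0.49 × (1.75 + 0.25k) / 2 / 0.70:

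- k = 0.5: 0.66
- k = 1: 0.70
- k = 1.5: 0.74
- k = 2: 0.79
- k = 3: 0.88

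**5. Person-time.** Full follow-up is 354 × 2 = 708 patient-years. If 25% leave evenly over 24 months, each loses one year on average: 354 × 0.25 × 1 = 88.5 patient-years. Only the part due to exits while still on PD could be recovered, and the documents do not split the 25% by reason.

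**The case against.** The strongest reply is that the cut-off is study withdrawal and that participants are permitted, not required, to withdraw. Someone who deviates or stops the product but stays in the trial can go on contributing data, in line with the abstract. This is correct. A reader might infer that everything after a deviation is discarded and that the analysis is therefore on-treatment. The text does not say so; that would follow only if every deviation were handled as a withdrawal, which the section leaves open.

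Three further inferences also lack support.

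- **That intention-to-treat and per-protocol nearly coincide.** The article does not define the per-protocol set. Which set decides the result may properly be left to the analysis plan.
- **That withdrawal will differ by arm because chlorhexidine irritates the skin.** The Background says only that it may irritate and could limit compliance, and calls the consequence uncertain. Ground (v) covers serious or suspected unexpected serious reactions, so mild irritation is not in itself a listed ground. The double-dummy design limits exits driven by knowledge of the arm, though not those driven by irritation.
- **That the bias could be put at 0.80.** That value, 1/(0.75 + 0.25 × 2), needs all leavers to go on day 0, from one arm, and treats the whole all-cause dropout as informative.

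It is also true that data cannot be collected after consent to data collection is withdrawn, and that an exit after the first infection costs the Cox analysis nothing.

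These points narrow the concern but do not remove it. For those who do withdraw under (i), (ii) or (v) while on PD, the rule still drops later infections under an intention-to-treat label, and no planned analysis is stated to repair that.

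**Conclusion.** The concern holds in this form: the Study withdrawal section does not separate stopping or deviating from the product from leaving follow-up, and its intention-to-treat rule ends at withdrawal. It conflicts with the abstract's follow-up rule and opens both primary analyses to informative censoring.

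The size and direction cannot be fixed from the documents. Spurious ratios of 0.86 to 0.91 (25% leaving one arm only, at month 6 or 12, with twice the rate) are illustrations. They would matter against a design ratio of 0.70, but they rest on assumed exit shares, timing and risk. The documents support neither a claim that the plan is an on-treatment analysis nor a claim that it favours a particular arm.

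**What to change.** Reconcile the abstract and the Study withdrawal section along these lines:

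- Distinguish discontinuing or deviating from the assigned product from withdrawing from follow-up. Who may stop the product is a clinical matter that this change leaves alone.
- For exits under (i), (ii) and (v), keep recording infections and PD time at the routine three-monthly PD clinic visits until PD ends, death, 24 months or withdrawal of consent to data collection.
- Define intention-to-treat as all randomised participants in their assigned arm, with all infections and PD time up to that point, and make per-protocol supportive.

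The cost is some extra record-keeping, consent to continued data collection, and dilution of the effect by non-adherence. The Trial status section reports 288 participants randomised by July 2019 with enrolment still open, so data on those who have already left may not be recoverable. Follow-up still to come can be protected.
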